**Safety endpoints**

Safety variables will be AEs spontaneously reported during the study e.g. falls, discontinuations due to AEs and vital signs indicating intolerance for locomotor practice (pulse rate, Rate of Perceived Exertion).

### Stopping rules and discontinuation

The criteria for termination of a training session include complaints of light-headedness or moderate or severe dyspnoea, or the development of paleness and excessive sweating or confusion; complaints of feeling ill; onset of angina; inappropriate bradycardia (drop in heart rate greater than 10 beats per minute). In addition, should the participant's HR exceed 80% of the predicted maximum HR (220 – age) or the participant report a Borg exertion rate of greater than 12–13, then the training ceases. Should training be halted, the participant is asked to rest (sitting or standing) while BP and HR are monitored and training will resume only when vital signs have returned to within an acceptable range and excessive dyspnea or chest pain have resolved. If any of these conditions persist after rest, the patient's primary physician is called and the patient referred for evaluation. If the patient complains of angina at rest, loss of consciousness occurs, or cardiac arrest, emergency medical services through 999 are called immediately. All therapists are CPR certified and aware of signs of cardiac complications.

Training sessions will also be halted in the event of a fall. All therapists are trained in first aid and manual handling and will assess the participant for injury. Should the fall be injurious and bone fracture, cardiac or neurological event is suspected, emergency medical services through 999 are called immediately. Should the fall be non-injurious the therapist will aide the participant to an upright position, monitor vital signs as outlined above and resume the training session if and when both the therapist and participant deem appropriate i.e. after rest or on the next planned treatment day.

For participants with poor proximal upper extremity muscle control, the hemiparetic arm may feel heavy and potentially painful during locomotor training. Additionally a heavy, flaccid upper-extremity can pull the trunk forward inhibiting good stepping. During training, the arm may be supported using a humeral cuff sling. If shoulder range is available and voluntary movement is present and pain-free, arm-swing is encouraged.

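### After a fall without injury, the protocol states no clear 999 step for a suspected neurological event with consciousness kept, or for a lesser suspected cardiac event

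*Protocol*

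**What the plan says.** The Protocol section "All therapists are trained in first aid and manual handling and will assess the participant for injury" comes from is Stopping rules and discontinuation; that sentence describes the only assessment stated after a fall. Two instructions follow it.

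- Emergency branch: "Should the fall be injurious and bone fracture, cardiac or neurological event is suspected, emergency medical services through 999 are called immediately".
- Non-injurious branch: "Should the fall be non-injurious the therapist will aide the participant to an upright position", then "monitor vital signs as outlined above and resume the training session if and when both the therapist and participant deem appropriate". The text adds that this may be after a rest or at the next planned session.

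The same section also has rules that do not depend on a fall or an injury.

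- General emergency triggers: "If the patient complains of angina at rest, loss of consciousness occurs, or cardiac arrest, emergency medical services through 999 are called immediately".
- A condition on restarting any halted session: "training will resume only when vital signs have returned to within an acceptable range and excessive dyspnea or chest pain have resolved".
- A list of symptoms that end a session, including "the development of paleness and excessive sweating or confusion". If the conditions persist after rest, the patient's "primary physician is called and the patient referred for evaluation".

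The section Trial Treatment / Intervention Related SAEs repeats the fall instructions, the general triggers and the restart condition. It does not repeat the symptom list.

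**The concern.** All participants are stroke survivors practising walking and turning. The Background cites a report that as many as half of stroke patients discharged into the community fall, and the Adverse Events section accepts a very small added risk of falling from walking practice. In this population a fall can accompany a new neurological or cardiac event and leave no injury. Whether the participant was hurt is then not the question that should decide the emergency call.

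As worded, the fall-specific 999 instruction joins injury and suspicion with a plain conjunction, and the only stated assessment is for injury. A therapist who follows the sentences in order finds no injury and arrives at a branch with no emergency step and no exception for a suspected event. The stake is participant safety in a small number of situations. Nothing in the trial's estimates depends on it.

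**Working it through.** No arithmetic applies. The check sets the instructions against each other and asks which cases are left without a stated 999 call.

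**Step 1: the fall sentences read literally.** 999 is called if the fall is injurious AND (fracture OR cardiac event OR neurological event is suspected).

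| Fall | Event suspected? | Instruction in the fall sentences |
|---|---|---|
| Injurious | Yes | 999 |
| Injurious | No | None stated |
| Non-injurious | No | Help up, monitor, resume at discretion |
| Non-injurious | Yes | Help up, monitor, resume at discretion; no 999 step |

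A suspected fracture is itself a suspected injury, so in practice the fourth row concerns suspected cardiac and neurological events.

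**Step 2: the looser parse.** The word for injury may be meant to go only with the fracture: 999 if (injurious AND fracture suspected) OR cardiac event suspected OR neurological event suspected. The fourth-row participant then meets the emergency sentence and also the non-injurious sentence, which carries no exception. The text does not say which governs.

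**Step 3: what the general rules cover.** Apply them to the fourth row.

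| Situation after a non-injurious fall | Rule that applies | 999 stated? |
|---|---|---|
| Cardiac arrest, loss of consciousness, or angina at rest | General triggers | Yes |
| Listed symptom, such as confusion, persisting after rest | Physician called, referral | No; physician route |
| Vital signs out of range, dyspnoea or chest pain unresolved | No restart; physician if it persists | No; physician route |
| Suspected neurological event, conscious, vital signs acceptable, no listed symptom | Non-injurious branch only | No |
| Suspected cardiac event short of the three triggers | Non-injurious branch, with the restart condition and physician route where they apply | No |

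The restart condition names vital signs, dyspnoea and chest pain. A conscious participant with a new neurological deficit could satisfy all of these.

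**Step 4: other places.** The SAE section repeats the fall wording, so it does not settle the question. No other section of the protocol gives a 999 instruction for the last two rows.

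**The case against.** The best defence is that the passage was never meant as strict logic. Read literally it also leaves an injurious fall with nothing suspected without any instruction, which points to loose drafting and not to a deliberate rule. The authors plainly had cardiac and neurological events after a fall in mind, since they name them. The likely intent is to separate serious falls, which go to 999, from harmless ones. A reader can also count any fall with a suspected event as injurious, and the gap disappears.

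Safeguards exist too. Restarting needs the agreement of therapist and participant and can wait for another day, so a therapist who suspects a stroke would not restart. Therapists are NHS staff, stay beside the participant, have first-aid and CPR training, and are said to know the signs of cardiac complications. Acute coronary syndrome and severe heart failure are exclusions.

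Most of this stands, and it limits the point. It does not remove it: the charitable reading is not written down, and none of the safeguards states a 999 call for the cases left over. The stated awareness of warning signs is cardiac only.

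A reader might infer three stronger claims that the protocol does not support.

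- That the two fall sentences necessarily contradict each other. They do not: a reading without conflict exists, and the non-injurious branch permits a restart without requiring one.
- That the protocol forbids or withholds an emergency call in these cases. It does not; it fails to state one.
- That the missing symptom list in the SAE section is a separate defect. That section is a repeat of the stopping rules, and the treatment section refers to the stopping rules for the criteria.

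**Conclusion.** The point holds as a minor participant-safety wording correction. Literally read, the fall-specific emergency call requires an injury, and the non-injurious branch has no exception for a suspected event. After the general rules are applied, two situations following an uninjured fall have no clearly stated 999 step: a suspected neurological event with consciousness kept, and a suspected cardiac event short of the three general triggers.

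The conclusion rests on the sentences as printed, which are the same in both sections. It assumes that a therapist may follow them in the order given. How many falls would be affected cannot be derived from the protocol. The practical risk is small, because trained staff would probably call 999 anyway. Sample size, outcomes and analysis are untouched.

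**What to change.** Reword the fall instructions in both Stopping rules and discontinuation and Trial Treatment / Intervention Related SAEs:

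- After any fall, injurious or not, call 999 immediately if a fracture, a cardiac event or a neurological event is suspected.
- Use the branch of helping the participant up, monitoring and possibly resuming only when the fall is non-injurious and none of these is suspected.

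The cost is a change of wording in two sections. Visits, data collection and analysis stay as they are.

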## RANDOMIZATION AND BLINDING

A total of 60 participants will be randomly assigned to one of three groups: overground visual cue gait training, treadmill based visual cue gait training or usual care walking practice. Participants meeting inclusion criteria will be referred for baseline assessment by the independent assessor and asked to give informed consent, after which randomisation will occur. The PI will obtain allocation by central telephone from the data management and analysis centre (University of Nottingham Clinical Trials Unit). The randomisation will be based on a computer generated pseudo-random code using random permuted blocks of randomly varying size,  created by the Nottingham CTU in accordance with their standard operating procedure (SOP) and held on a secure server. Block randomisation will be used to stratify participants into two groups according to gait speed (Severe group: <0.4 m/s; Moderate group: between 0.4 m/s and 0.8 m/s) to obtain balanced groups on severity.

Access to the sequence will be confined to the CTU Data Manager and the PI.  Investigators will access the treatment allocation for each participant by means of a remote, internet-based randomisation system developed and maintained by the Nottingham CTU. The sequence of treatment allocations will be concealed until interventions have all been assigned and recruitment, data collection, and all other trial-related assessments are complete. The independent assessor will be blinded to treatment allocation. The assessor will record a guess of participants’ group allocation for later examination of the success of masking. Therapists and participants will not be blinded to allocation.

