# ABBREVIATIONS

Add to / amend accordingly

| ADR | Adverse Drug Reaction |
| --- | --- |
| AE | Adverse Event |
|  |  |
| CI | Chief Investigator overall |
|  |  |
| CRF | Case Report Form |
|  |  |
| DAP | Data Analysis Plan |
| DMC | Data Monitoring Committee |
|  |  |
|  |  |
| EOT | End of Trial |
|  |  |
| GCP | Good Clinical Practice |
|  |  |
| ICF | Informed Consent Form |
|  |  |
|  |  |
|  |  |
| NHS | National Health Service |
|  |  |
| P/GIS | Parent / Guardian Information Sheet |
| PI | Principal Investigator at a local centre |
| PIS | Participant Information Sheet |
|  |  |
| REC | Research Ethics Committee |
| R&D | Research and Development department |
|  |  |
| SAE | Serious Adverse Event |
|  |  |
| SPC | Summary of Product Characteristics |
|  |  |
|  |  |
| TMG | Trial Management Group |
| TSC | Trial Steering Committee |

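### The PI may see the randomisation sequence and also obtains each allocation, so allocation is not concealed from someone who triggers randomisation and may recruit

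*Protocol*

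**What the plan says.** Four statements in the protocol's RANDOMIZATION AND BLINDING section bear on concealment.

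- On requesting an allocation: "The PI will obtain allocation by central telephone from the data management and analysis centre".
- On who may see the list: "Access to the sequence will be confined to the CTU Data Manager and the PI".
- On concealment: "The sequence of treatment allocations will be concealed until interventions have all been assigned", and until recruitment, data collection and the remaining assessments are finished. The sentence does not say from whom.
- On a second route: "Investigators will access the treatment allocation for each participant by means of a remote, internet-based randomisation system".

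The sequence uses "random permuted blocks of randomly varying size" within two gait-speed strata. No site stratum is mentioned. On masking, "Therapists and participants will not be blinded to allocation", while the independent assessor is blinded and records a guess of each participant's group.

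The ABBREVIATIONS list defines PI as "Principal Investigator at a local centre". Elsewhere the term seems to mean one lead person: TRIAL MANAGEMENT names a single PI on the steering committee, and the text on standardising the interventions has the PI visiting every site.

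**The concern.** Concealment means that nobody who can influence whether or when a patient enters knows the next assignment. The protocol gives list access to the role that requests allocations. Someone who knows the next assignment could bring an entry forward, hold it back or decline it.

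Two results of the pilot are exposed. The first is the comparison between arms: the synopsis plans a difference in proportions with 95% confidence limits, and the objectives use the outcomes to size the definitive trial. The second is the feasibility data: the number of patients willing to be recruited is a primary endpoint, and it would be distorted if eligible patients were turned away because of the arm due next. Since treatment is known to therapists and participants, concealment before entry is the main safeguard against selection. Assessor blinding protects measurement, not entry.

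**Working it through.** The check is mainly textual. The protocol states no figure to reproduce.

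**1. Access and request set side by side.** The PI is one of two roles with access to the sequence, and the PI obtains the allocation. Nothing elsewhere in the protocol withdraws either statement. The section on maintaining the randomisation codes deals with concealment from the independent assessor, which is a different matter.

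**2. Who the PI is.**
- If PI means local-centre investigator, as the ABBREVIATIONS list says, list access may extend to every site.
- If PI means the trial lead, that person helps to train therapists and visits the sites. The lead may also be among the senior research team members who, under Recruitment and Informed consent, identify volunteers from previous studies or approach patients.

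Neither reading places the role clearly outside recruitment.

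**3. What the other safeguards cover.** Varying block sizes, a secure server and central allocation prevent guessing. They still work against the nurses, therapists and research associates who identify and consent patients. They do not work against a person who can read the list. Baseline assessment before randomisation does not prevent entry being delayed or declined.

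**4. Predictability.** With three equal arms and full concealment, the chance of naming the next arm is about 1 in 3. A list holder who also knows the current position in the relevant stratum can name it with certainty. The protocol does not say whether the PI sees that position.

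**5. Illustration of size.** From the protocol: 20 participants per arm (synopsis). Assumed: an average success proportion of 30%, two likely responders steered into one VCT arm, and two likely non-responders steered into usual care (4 of 60 entries), each in place of an average patient.

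Shift = 2 × (p_R − 0.30)/20 + 2 × (0.30 − p_N)/20, where p_R and p_N are the success probabilities of the steered patients.

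- Perfect prognosis (p_R = 1, p_N = 0): 2 × 0.70/20 + 2 × 0.30/20 = 0.07 + 0.03 = 0.10.
- Imperfect prognosis (p_R = 0.50, p_N = 0.10, also assumed): 2 × 0.20/20 + 2 × 0.20/20 = 0.02 + 0.02 = 0.04.

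For scale, the 95% half-width for a difference at 30% in both arms is 1.96 × √(2 × 0.30 × 0.70/20) = 1.96 × 0.145 ≈ 0.28.

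**The case against.** The strongest defence is that the protocol does not make the PI the recruiter. Clinicians, therapists and network nurses identify patients. A senior team member, research associate, research nurse or research therapist approaches them. The independent assessor does the baseline assessment, and the PI's stated step comes after consent and baseline. This stands. A reader might infer that the list is open to *the person enrolling patients*. The documents support only the narrower statement that it is open to the person who obtains allocations and who may take part in recruitment.

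A reader might also infer an outright contradiction. The concealment sentence names no audience, so it can be read as covering everyone except the two roles just given access. That reading removes the contradiction but leaves the access in place.

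Third, if the PI is a local investigator, the absence of a site stratum means that knowing the next slot requires knowing the position across all sites. Certain prediction is therefore an assumption.

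Fourth, this is a pilot with no formal testing. The 10-point shift assumes perfect prognosis, and even then it is small beside an interval of about ±28 points. Both facts are right. They limit the practical damage to the comparison, but a wide interval describes sampling error and does not make a selection bias disappear.

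Finally, delaying or re-ordering entries does not change the total recruited, and refusals at consent precede randomisation. So the recruitment counts are at risk only if eligible patients are declined.

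**Conclusion.** The point holds in a limited form. As written, the protocol does not conceal the sequence from a role that triggers randomisation and may be involved in recruitment, and this fits poorly with its own concealment statement. The consequence is an avoidable risk of selection bias in the between-arm estimates and, where eligible patients are declined, in the recruitment counts.

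The documents do not show that such selection would occur, nor how large it would be. The 10-point figure is a worst case: it needs four steered entries, 20 per arm, 30% average success, perfect prognosis and knowledge of the list position. Under the milder assumed prognosis the same four entries give 4 points.

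Two stronger inferences are not supported. Random blocks and central allocation are not useless, since they still protect against every recruiter without list access. Nor is the trial open to everyone, since the outcome assessor is blinded.

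**What to change.** Replace the access sentence in RANDOMIZATION AND BLINDING with wording to this effect: only clinical trials unit staff with no part in recruitment may see the sequence, and no investigator or member of a site or trial team may see it before recruitment and data collection have finished.

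State that allocations are released singly, each after consent, eligibility and baseline data have been recorded. Much of this is already there: randomisation already follows consent and baseline, and the internet system already works participant by participant.

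Reconcile the two routes. The synopsis and the first paragraph of the section give central telephone, while the second paragraph gives an internet system. State which applies, or how they fit together, and say whether PI means the trial lead or a local investigator.

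The cost is a few sentences and the removal of an access right on the server. No function described in the protocol needs the PI to hold the full list. The change should be made before recruitment, because selection at entry cannot be repaired in the analysis.

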### Maintenance of randomisation codes and procedures for breaking code

Allocation will be concealed from the independent assessor. However, it is not possible to mask the treating therapists or participants. We will follow guidelines to improve independent assessment in rehabilitation trials ([Siemonsma and Walker 1997](#_ENREF_41)), which include practical measures such as locating treating therapists and assessors in separate locations and instructing participants not to tell the assessor which treatment they have been assigned to.

The assessor will record a guess of participants’ group allocation for later examination of the success of masking

1. We have carried out a risk / benefit analysis of the all aspects for the study and found that overall the study is a low risk study. The only aspects of the study that raised a medium level of risk were:
   1. An increased risk of falling outside the house. We will specifically record this adverse event in the group who receive both the experimental and control interventions. The level of falls can be easily assessed by the TSC and a decision made regarding participant ethical and safety concerns.
   2. Implementation of the treatment - obtaining agreement from the PCTs to fund the treatment could be difficult, participants may not then receive the experimental intervention as planned
   3. Maintaining blinding (The research assistant will be blind to treatment allocation. However, as they are required to visit participants to complete the assessments, the participant may discuss what has been happening and therefore un-blind the research assistant). We will monitor this effect
   4. Collection of identifiable data for the Medical Research Information Services. We will be using this system to check if a participant is alive before we send any questionnaires. We will follow Research Governance procedures when collecting this information.
   5. Incomplete data, especially from questionnaires. We are using a Clinical trial Unit to collect and store data and to check weekly for incomplete data. We have a policy for increasing the rate of completion that will be followed
2. The pace of recruitment is anticipated to be very swift. If this is the case then the timescale to analyse the data and adjudicate as to proven effectiveness or otherwise of the intervention would mean that most, if not all, participants would already have been recruited by the time such a decision was reached.

[name] (University of Salford) has agreed to be the independent chair of the TSC & DMEC. We have also enrolled [name] (for independent scientific expertise on visual cueing and locomotor control) [name] as a patient representative and [name] (Senior Statistician, University of Glasgow as independent statistician), along with [name] (PI).

Schedule of meetings:

During the first work package fortnightly project meetings involving the grant holders will take place to manage the development phase. Three meetings will be scheduled to form the treatment manuals.

The TSC & DMEC committee will meet three times during the project, (1) towards the end of the ‘project preparation’ work package (month 5) to evaluate the results of the development phase, (2) at the mid point of the recruitment period (month 12) to assess recruitment rates and review general progress and (3) after the data analysis is complete (month 23) to discuss results and dissemination.

| Work Package |  | **Months** | | | | | | | |  |  |  |  |  |  |
| --- | --- | --- | --- | --- | --- | --- | --- | --- | --- | --- | --- | --- | --- | --- | --- |
|  |  | -3 | 0 | 1 | 2 | 3 | 4 | 5 | 6 | 9 | 12 | 15 | 18 | 21 | 24 |
| Prepratory work package |  |  |  |  |  |  |  |  |  |  |  |  |  |  |  |
|  | LREC approval |  |  |  |  |  |  |  |  |  |  |  |  |  |  |
|  | Design of VCT software |  |  |  |  |  |  |  |  |  |  |  |  |  |  |
|  | *Fortnightly grant holder’s meetings* |  |  |  |  |  |  |  |  |  |  |  |  |  |  |
| Package one:  Project development phase |  |  |  |  |  |  |  |  |  |  |  |  |  |  |  |
|  | Development of treatment manuals |  |  |  |  |  |  |  |  |  |  |  |  |  |  |
|  | Identify/train therapists to deliver treatment |  |  |  |  |  |  |  |  |  |  |  |  |  |  |
|  | Finalise light cue procedures |  |  |  |  |  |  |  |  |  |  |  |  |  |  |
|  | Define GAITRite measurements |  |  |  |  |  |  |  |  |  |  |  |  |  |  |
|  | Liason SRN |  |  |  |  |  |  |  |  |  |  |  |  |  |  |
|  | Prepare cost recordings |  |  |  |  |  |  |  |  |  |  |  |  |  |  |
|  | *TSC meetings* |  |  |  |  |  |  |  |  |  |  |  |  |  |  |
| Package Two: Project Implementation |  |  |  |  |  |  |  |  |  |  |  |  |  |  |  |
|  | Recruit Participants |  |  |  |  |  |  |  |  |  |  |  |  |  |  |
|  | Deliver Treatment |  |  |  |  |  |  |  |  |  |  |  |  |  |  |
|  | Perform outcome assessments |  |  |  |  |  |  |  |  |  |  |  |  |  |  |
|  | *TSC meetings* |  |  |  |  |  |  |  |  |  |  |  |  |  |  |
| Package Three: Data analysis and write up |  |  |  |  |  |  |  |  |  |  |  |  |  |  |  |
|  | Analyse data |  |  |  |  |  |  |  |  |  |  |  |  |  |  |
|  | Write manuscripts |  |  |  |  |  |  |  |  |  |  |  |  |  |  |
|  | *DMEC meetings as required* |  |  |  |  |  |  |  |  |  |  |  |  |  |  |

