### Criteria for terminating trial

Termination of the trial as a whole may be the result of poor recruitment or safety concerns should falls or other AEs be heavily prevalent in either treatment arm. However, the treatment is considered to be low risk and termination of the trial due to AEs is not anticipated.

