# ADVERSE EVENTS

There may be a very small increased risk of falling as a result of walking practice and this small risk is stated clearly in the patient information sheet. Every effort will be made to minimise the risk of falls through training the patient and having therapists next to patients at all times. We do not expect any other risks of taking part in the study. Therefore, it is reasonable to collect only targeted treatment-related adverse events and serious adverse events such as ‘falls leading to injury requiring a hospital or GP visit’. Should such an event occur, an adverse event form (Appendix 11) will then be completed by the relevant therapist (forms can also be downloaded from the trial website). Participant fatigue which requires only momentary rest and following which the training session resumes will not be classed as an adverse event and will not require reporting but will be documented through any resulting reduction in treatment time.

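### The trial relies on its steering committee judging the level of falls, but no described procedure asks about falls, three sections disagree on which falls count, and only serious events are routed to the committee

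*Protocol*

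**What the plan says.** Trial Management, under the steering and monitoring committees, explains why the steering committee (TSC) can also act as the data monitoring and ethics committee (DMEC). The study is rated low risk overall, and five aspects are listed as medium risk. The first reads: "An increased risk of falling outside the house. We will specifically record this adverse event", and this is to apply to experimental and control participants. The protocol adds: "The level of falls can be easily assessed by the TSC".

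Criteria for terminating trial names poor recruitment and "safety concerns should falls or other AEs be heavily prevalent in either treatment arm" as grounds for ending the trial, while saying that termination for adverse events is not expected.

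Three sections describe which falls are collected:
- Safety endpoints: "Safety variables will be AEs spontaneously reported during the study e.g. falls". There is no restriction by injury or place.
- Trial Management: falls outside the house, recorded specifically.
- Adverse Events: "it is reasonable to collect only targeted treatment-related adverse events and serious adverse events such as" falls whose injuries need hospital or GP attention. When such an event occurs, "an adverse event form (Appendix 11) will then be completed by the relevant therapist".

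Assessment of Safety plans no dedicated safety assessment and sends serious adverse events, and nothing else, to the TSC & DMEC each quarter.

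**The concern.** The oversight arrangement rests on a committee that can see how often participants fall, in each arm, and act on it. That needs three things: a definition of which falls count, someone who asks about or records them throughout follow-up, and a route from the record to the committee. The protocol disagrees with itself on the first and gives no working version of the other two for a non-serious fall.

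Such a fall, outdoors and between sessions, is just what the risk assessment singles out. It may reach the trial only if the participant mentions it, usually to a therapist who knows the allocation. Even if it is written down, no section says that the committee sees it. A low count could then be read as reassurance when it reflects only that nobody asked. Because the named recorder is unblinded, willingness to mention or note a fall could also differ between arms. An analysis plan cannot repair this, since it cannot recover events that were never collected.

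**Working it through.** No stated figure needs reproducing. The check sets the sections side by side and does one piece of exposure arithmetic.

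**1. Which falls count.** Take an uninjured fall in the street between sessions.
- Under Safety endpoints it counts if the participant volunteers it.
- Under Trial Management it must be recorded.
- Under Adverse Events it does not clearly qualify: it is not serious, and whether it is treatment-related is left to judgement.

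No section says which of the three prevails.

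**2. Who asks.** Each scheduled contact or form was searched for a falls question.
- Table 1: no falls item at baseline, post-intervention or 3 months.
- Falls Efficacy Scale (Secondary endpoint): measures confidence, not falls.
- Self-report log (Trial / Study Treatment and Regimen): described as recording minutes of outside physical and occupational therapy.
- Health economic analysis: resource use is limited to care specific to stroke rehabilitation.
- Stopping rules and discontinuation, and Trial Treatment / Intervention Related SAEs: describe handling a fall in a session, but not recording a non-injurious one.

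**3. Who records, and for how long.** The adverse event form is the therapist's. Treatment lasts 8 weeks and the last assessment is 3 months after randomisation (Table 1).
- 3 months = 91.3 days; 91.3 / 7 = 13.0 weeks.
- 13.0 − 8 = 5.0 weeks after treatment.
- 5 / 13 = 38% (39% with unrounded weeks).

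In that window no trial session is scheduled and no recorder is named. The remaining assessments belong to the blinded assessor. Table 1 schedules the log at 3 months, but the section describing it has it returned to the intervention therapist during the intervention period.

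**4. What the committee receives.** Serious events each quarter (Assessment of Safety), and three meetings at months 5, 12 and 23 (Trial Management). Recruitment runs over months 6 to 18 in that section, so one meeting falls within it. No section routes a non-serious fall to the committee.

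**5. Can the share of missed falls be computed?** No. The protocol gives no proportion of falls that need medical attention. The background figure of up to 50% counts people who fall and has no time window. For range only, assume a constant fall rate and an injurious share q of 10% to 75%:
- Injurious falls recorded during treatment only: captured share = q × 8 / 13.04. This gives 6% at q = 10%, 15% at 25%, 31% at 50% and 46% at 75%.
- Injurious falls recorded over all 3 months: captured share = q, that is 10% to 75%.
- If Safety endpoints governs and every fall is volunteered, nothing is lost.

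The answer depends on which section is followed and on an assumed q.

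**The case against.** A reader might infer that the trial collects only injurious falls, that most falls are lost, and that every fall after treatment goes unrecorded. The text supports none of these:
- The injurious fall in Adverse Events is introduced as an example, and Safety endpoints admits any volunteered fall.
- Safety endpoints covers the whole study, and a 3-month visit exists at which a fall could be mentioned.
- The adverse event form (Appendix 11) is not shown, so it may ask for place and injury.
- Table 1 is a schedule of outcome measures and lists no adverse events of any kind, so a missing falls row is weak evidence by itself.

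The defence can add that this is a 60-person feasibility pilot in which fall incidence is neither an objective nor an outcome. The same therapists deliver the treatments, and the number and length of sessions are matched. No difference in capture between arms has been shown, and the post-treatment 38% is a share of time, not of falls.

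All of this stands against the stronger readings. It does not supply what is missing. A form completed once an event is known does not find events, a volunteered fall is not an actively sought one, and matched contact does not remove the therapist's knowledge of allocation. Nor does pilot status answer the point, because the protocol itself makes falls a possible reason to stop and part of its case against a separate DMEC.

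**Conclusion.** The point holds as an internal conflict combined with passive collection. Safety endpoints, Trial Management and Adverse Events give three different scopes for falls. No scheduled visit and no described log content asks about them. No recorder is named for about 5 of 13 weeks per participant. Non-serious falls have no stated route to the committee meant to judge them. Followed as written, the TSC & DMEC could lack the data on which the risk assessment and the termination criterion depend.

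The size can be given only as exposure time (38% of follow-up without a named recorder), not as a proportion of falls missed. Differential capture between arms is a possibility arising from unblinded recorders, not a demonstrated bias. The conclusion assumes that 3 months is about 13 weeks and that the unseen appendices add no active falls question beyond what the body of the protocol describes.

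**What to change.** 1. Reconcile Safety endpoints, Trial Management, Criteria for terminating trial, Assessment of Safety and Adverse Events so that they state one scope for the falls to be recorded. The statement under Definition of Population Analysed that safety summaries are unnecessary should be worded to allow step 4.
2. Add a falls item (date, place, injury) to the existing self-report log, in all three arms, from randomisation to the 3-month visit at which Table 1 already schedules the log.
3. After treatment ends, have the log returned to the trials unit, not handed to the assessor, so that assessor blinding is protected. This also names a recipient for the last 5 weeks.
4. Report fall counts by arm to the TSC & DMEC with the quarterly report of serious adverse events.

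The cost is a protocol amendment, one line on a form already in use and slight extra burden for participants. The reported number of falls will rise because falls are being asked about, and the committee should be told to expect this. The change concerns recording and reporting only. How a fall is managed, and what level of falls would end the trial, remain for the sponsor to set.
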